**Fig. 1 Fig1:**
[figure not shown]
Project timeline

At month 4, ICU teams will commence the protocolised review in their ICU. The Champion will have access to the online enhanced CQR reports, and the online education material will remain available to all ICU team members. Online support for troubleshooting relating to the implementation strategies will be available to the Champions. In addition, voluntary monthly group sessions will be facilitated by the project team from months 4–6, whereby Champions, RAs and other team members will be welcome to join to reflect on their experience and share learning between sites. Daily data collection (CQR and E-CRF) will continue throughout this period. Champions will be interviewed during months 4–6 to explore barriers and facilitators to implementation, adaptations made to both the intervention and its implementation, along with perceptions regarding likely adoption and maintenance (Supplementary File 3).

At the end of month 6, the implementation strategies of online education, the role of Champions, and the RA collecting daily data on review processes will cease. The daily auditing of whether reviews take place will be transferred to the CQR data collectors and reported monthly as part of the CQR report. A second interview will be conducted with Champions following month 6 to explore barriers and facilitators to adoption, and adaptations to the intervention made post-implementation (Supplementary File 4).

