### Data collection

Data regarding case mix (including source and reason for admission, severity of illness at admission, comorbidities) along with physiology, organ support, antimicrobial prescriptions and microbiology data, care processes (duration of antimicrobials) and clinical outcomes will continue to be collected daily through the existing CQR during months 1–8. The CQR data collectors will also collect adoption and reach of any pre-existing structured review during months 1–2.

A project specific E-CRF on REDcap [52, 53], will capture data on antimicrobial reviews during months 4–6 (see Table 1 above). This additional E-CRF collection will be done by the RAs. Copies of existing antimicrobial guidelines will be requested prior to commencement of the study, and ICU stakeholders’ perspectives regarding the current guidelines, along with information on existing antimicrobial stewardship activities already present in the ICU captured during the site onboarding by Champions. Changes in guidelines made during the project will also be captured, and the current working version of the guidelines queried at each phase of the project. Post implementation (months 7 onwards), the CQR data collection will continue, along with a measure of adoption.

Qualitative data exploring the Champions’ perspectives regarding implementation, acceptability, adoption and maintenance, along with contextual factors influencing implementation will be collected through semi-structured interviews at two time points during the study: implementation (months 4–6) and post-implementation (month > 6). We intend to interview all Champions during both phases but recruitment may cease if concurrent analysis indicates that theoretical saturation has been achieved. Interviews will be conducted remotely using the Zoom (Zoom Video Communications Inc, San Jose, CA, USA) conferencing application. A participant information sheet (Supplementary File 5) will be provided and verbal consent for participation sought (Supplementary File 6). In addition, Champions together with RAs will be requested to maintain an implementation log [54], whereby adaptations, and observed barriers and facilitators to implementation will also be reported. These will be reviewed and thematically coded alongside the interview data.

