#### Statistics

For the primary outcome, we will describe the proportion of ICUs that achieved ≥ 80% of all three indicators (fidelity, reach and adoption). We will also report these indicators separately. We will compare the proportion achieved in the post-implementation period, as specified in the Table 2, with the baseline assessment, using a McNemar test (Chi-square for repeated measures).

**Table 2 Tab2:** Outcomes

**Outcome**	**Measure and reporting**
Implementation (Primary Outcome)	**Fidelity: **The proportion of prescriptions reviewed as intended (review at 48hrs with documentation of all 4 review components: indication, route, duration and stop date). Reported as a proportion of the number of possible reviews during months 4-6. Numerator: Number of reviews conducted as intended Denominator: Number of prescriptions of antimicrobials Expressed as a %. Binary outcome: success/fail, 80% is threshold. Proportion of weekly A&F report meetings held from month 4 until the time of adoption (Number of meetings/12, expressed as a %) (not in composite outcome)
	**Reach: **Proportion of eligible patients who received a review during months 4-6 Numerator: Number of patients that received at least 1 prescription review Denominator: Number of eligible patients Expressed as a % Binary outcome: success/fail, 80% is threshold. Proportion of eligible staff that receive education (expressed as a %; eligible staff defined prospectively by Champion) (not in composite outcome)
	**Adoption**: Proportion of prescriptions reviewed as intended during month 7 Numerator: Number of prescriptions of antimicrobials reviewed Denominator: Number of prescriptions of antimicrobials Expressed as a % Binary outcome: success/fail, 80% is threshold.
Intervention effectiveness (secondary outcomes)	**Appropriateness of prescriptions:** Antimicrobial Density (AD) Duration of Therapy (DOT) Antimicrobial Redundancy Rate (ARR)
	**Antimicrobial care processes:** Does the drug Duration exceed the Stop date? Antimicrobial resistance rate (% of patients that have an multidrug resistant pathogen identified) Antimicrobial prescribing rate (% of all patients) Count of cultures taken and reported as a proportion of the population on antimicrobials.

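### Adoption, which an ICU must pass to count as a success, is titled as complete, timely review, but its numerator counts any review, and the month-7 data described match only the numerator

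*Protocol article*

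**What the plan says.** Table 2 (Statistics section) gives three indicators for the primary outcome, each with an 80% threshold, and the Statistics text counts an ICU as successful only if it reaches 80% on all three.

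- **Fidelity, months 4–6.** A review as intended is "review at 48hrs with documentation of all 4 review components: indication, route, duration and stop date". The calculation keeps that condition: "Numerator: Number of reviews conducted as intended Denominator: Number of prescriptions of antimicrobials".
- **Adoption, month 7.** "Proportion of prescriptions reviewed as intended during month 7 Numerator: Number of prescriptions of antimicrobials reviewed". The denominator is again all antimicrobial prescriptions.

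On where the data come from:

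- Implementation procedure: at the end of month 6, "the RA collecting daily data on review processes will cease". From then on, "The daily auditing of whether reviews take place will be transferred to the CQR data collectors".
- Data collection: the project E-CRF "will capture data on antimicrobial reviews during months 4–6". From month 7 the section promises continued registry data and an adoption measure whose fields it does not list.
- Table 1: the only addition to the monthly registry reports beyond month 6 is the share of prescriptions reviewed. The share reviewed within 48 hours is a separate item, listed for months 4–6 only.

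**The concern.** The title and numerator of one primary-outcome indicator describe different quantities. The Fidelity row shows that the authors write the timing and completeness condition into a numerator when they mean it, so its absence from the Adoption numerator cannot be passed over as shorthand.

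Adoption carries weight because it is a necessary condition for success. It is also measured just after the Champion role, the education and the research assistants' data collection have ended, and the Limitations section says implementation is not followed beyond month 7. It is therefore the one quantitative indication of what remains once support is withdrawn. If any review counts, an ICU could pass while the complete, timely review it was asked to adopt has slipped below 80%, and the title would hide this from the reader.

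The same term is used at entry. Under Site selection criteria, an ICU that already has a structured review with adoption and reach of 80% or more in months 1–2 is not eligible. The reading chosen can thus affect who enters as well as who succeeds.

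**Working it through.** **The plan's own size figure.** Recruitment gives a median of 40 admissions per month per ICU, with 75% receiving antimicrobials: 40 × 0.75 = 30 eligible patients per month, × 6 = 180 per ICU, × 35 = 6300. This reproduces the stated 180 and about 6300. Month 7 therefore has about 30 eligible patients in a median ICU.

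**Two readings.** Let r be the share of month-7 prescriptions that get any review, and c the share of those reviews that are on time with all four components documented. The protocol gives neither, so both are assumptions.

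- Adoption by the numerator = r
- Adoption by the title = r × c

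Since r × c cannot exceed r, disagreement runs one way only: the numerator passes and the title fails. It occurs when r ≥ 0.80 and c < 0.80 / r.

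| r (any review) | Smallest c for the title also to pass (0.80 / r) |
|---|---|
| 80% | 100% |
| 85% | 94.1% |
| 90% | 88.9% |
| 95% | 84.2% |
| 100% | 80% |

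Examples on both sides:

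- r = 85%: c = 70% gives 0.85 × 0.70 = 59.5% (fail); c = 90% gives 76.5% (fail); c = 95% gives 80.75% (pass).
- r = 90%: c = 70% gives 63% (fail); c = 85% gives 76.5% (fail); c = 90% gives 81% (pass).
- r = 95%: c = 80% gives 76% (fail); c = 85% gives 80.75% (pass).

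**Chance that one ICU reaches 80%.** Assume 1 to 2 prescriptions per eligible patient (30 to 60 in month 7), r = 90%, and independent prescriptions. The chance is the binomial probability of at least 24 of 30, or at least 48 of 60.

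| Reading | 30 prescriptions | 60 prescriptions |
|---|---|---|
| Numerator, p = 0.90 | 97.4% | 99.4% |
| Title, c = 95%, p = 0.855 | 86.6% | 91.3% |
| Title, c = 85%, p = 0.765 | 42.1% | 32.1% |

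**Which ICUs are affected.** The reading changes the composite only where Fidelity and Reach are already passed. Counting one qualifying review per prescription, passing Fidelity means r × c ≥ 0.80 in months 4–6, so c was at least 80% then. An ICU with 90% reviewed that just met Fidelity had c = 0.80 / 0.90 = 88.9%; a fall to 85% in month 7 with r unchanged gives 76.5%, which fails by the title and passes by the numerator. An ICU at 95% on both (0.95 × 0.95 = 90.25%) would need c to fall below 84.2% before the readings parted.

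**The case against.** The strongest reply is that the evidence is not evenly split. The numerator, the Table 1 item beyond month 6 and the description of the month-7 audit all describe any review; the title's qualifier is the outlier, and deleting it would make the plan consistent. That stands, and it is why retitling is one of the two fixes below. It does not remove the conflict as printed, and it leaves Adoption a looser measure than Fidelity.

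A reader might infer that month 7 will record nothing but whether a review occurred, so that the titled measure cannot be computed. The protocol does not support that. The post-implementation adoption measure is unspecified, Strategy 2 gives no end date for reporting the four components, and the section on feasibility of collecting outcomes says the four steps will be recorded without limiting the period. What can be said is that no section assigns timing or component capture to month 7. The Statistics section also promises code lists and indicator definitions before data collection. These are not shown and may settle the matter, but they would still have to override one half of Table 2.

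A reader might also fault the change from research assistants to registry collectors. It follows from withdrawing support, and registry collectors also gather adoption and reach in months 1–2, so the planned comparison with baseline has the same type of collector at both ends. No test of Adoption against Fidelity is planned, and the indicators are also reported separately.

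Finally, the size depends on assumed rates. At high completeness both readings pass, and an ICU that fails Fidelity fails the composite under either.

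**Conclusion.** The inconsistency is real and lies inside the primary outcome. Adoption has two definitions in one table cell, and the month-7 data described fit the looser one. For ICUs that pass Fidelity and Reach, the choice can turn a success into a failure whenever month-7 completeness falls below 0.80 / r: about 94%, 89% and 84% at assumed any-review rates of 85%, 90% and 95%.

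The number of ICUs affected cannot be estimated from the protocol, which gives neither rate. The pass probabilities also rest on an assumed 30 to 60 prescriptions and on independence between them. Two stronger readings are not supported. Adoption is not a one-third weight; it is one of three necessary conditions. Nor does it follow that the trial will report sustained uptake where complete review has collapsed. It could do so, but only in ICUs where completeness had been at least 80% in months 4–6 and then dropped below the limit above.

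**What to change.** Settle the definition before data collection, because timing and component fields not captured in month 7 may not be recoverable. Either option resolves the conflict.

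1. **Keep the title.** Set the Adoption numerator to prescriptions reviewed as intended, by the Fidelity rule. Add review time and a yes/no field for each of the four components (five fields) to the registry form for month 7 and for the months 1–2 baseline with which it is compared. The cost is a little more data entry for existing collectors, in up to 11 registries, and possibly a lower adoption figure.
2. **Keep the numerator.** Drop the qualifier, title Adoption as any review, and report the any-review rate for months 4–6 beside it, so that month-7 Adoption is compared like for like and not read as sustained complete review. This changes Table 2 and adds one descriptive figure. The cost is a weaker claim about what persists after support ends.

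Under either option, state that the adoption figure used for site eligibility in months 1–2 follows the same definition.

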#### Conduct of review

Participating ICU teams will be required to undertake a structured review of each antimicrobial prescription for all patients receiving antimicrobials. Reviewing prescriptions allows their appropriateness to be reconsidered in the context of emerging clinical and/or microbiological data [37]. The review should be completed within 48 h of a new prescription being commenced, or at ICU admission where pre-ICU antimicrobial prescriptions exist. The review will necessitate documentation of the four key steps as defined by the WHO: indication (in relation to pre-existing local guidelines), route (e.g. parenteral or enteral), expected duration of therapy and intended stop date (including escalation or de-escalation discussions). It will also necessitate documentation of any changes (or lack thereof) made to the prescription, including: the choice of drug, route of administration and duration of treatment. The reviewing ICU team will consider the choice of therapy in relation to the known or assumed indication, the dose in relation to local ICU antimicrobial guidelines, the route of administration, and whether escalation to parenteral, or de-escalation to enteral route (and related dosing and duration adjustments) are warranted. Given the rapidly changing clinical status of critically ill patients, and emerging clinical and/or microbiological data during the ICU stay, it is anticipated that patients may receive more than one review during their ICU encounter. ICUs’ existing antimicrobial guidelines for the management of infections in critically ill patients will be utilised.

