For the secondary outcomes, we will perform an interrupted times series analysis. We will observe the weekly temporal resolution of each indicator and set the model to account for the natural/secular time trend, implementation of the intervention (level change) and the trend after implementation (slope change). We will account for auto-correlations. The model applied will depend on the data, but we will evaluate ARIMA models, segmented regressions and Holt-Winters additive model to evaluate the best model for the times series. Counts of actions recorded in response to the review will be described. The code lists for the primary and the secondary outcomes, and definitions for indicators of quality will be developed and published in advance of data collection.

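### The interrupted time series is applied to the stop-date overrun indicator, for which the protocol provides no complete or comparable pre-implementation series

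*Protocol article*

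**What the plan says.** Table 2 places "Does the drug Duration exceed the Stop date" among the antimicrobial care processes, under intervention effectiveness. It gives no denominator.

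The Statistics section then says: "For the secondary outcomes, we will perform an interrupted times series analysis". It continues: "We will observe the weekly temporal resolution of each indicator". The model is to carry a secular trend, a level change at implementation and a slope change afterwards. No indicator is excepted.

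On where the stop date comes from and when it is recorded:

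- **Conduct of review**: the review has to document, among other items, "expected duration of therapy and intended stop date (including escalation or de-escalation discussions".
- **Implementation procedure**: "At month 4, ICU teams will commence the protocolised review in their ICU". After month 6, "the RA collecting daily data on review processes will cease", and the registry collectors then audit only whether reviews happen.
- **Data collection**: the project E-CRF "will capture data on antimicrobial reviews during months 4–6". The registry items named for months 1–8 include prescriptions and duration, but not a stop date. For the first two months the section adds only reach and adoption of any review already in use.
- **Table 1**: the audit items collected throughout the project include documented indication, but not stop date.
- **Implementation procedure**, on the other side: baseline data in months 1–3 are said to come from the registry, the E-CRF and the site survey.

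**The concern.** A level change and a slope change are contrasts with a pre-implementation series. For this indicator, the item that defines the outcome is itself a product of the intervention. The protocol therefore assigns a before-and-after model to a measure for which its data plan names no before.

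If some baseline stop dates do turn up, a second difficulty follows. Overrun can be assessed only for prescriptions with a recorded stop date. Recording it is one of the four components of fidelity, which has an 80% success threshold, so the set of prescriptions that can be assessed is meant to change at the interruption. A step in the series could then reflect which prescriptions became assessable, not how closely stop dates were kept. At stake is an effectiveness estimate that either cannot be produced or can mislead.

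**Working it through.** **The plan's own figures.** The Recruitment section gives the only size figures: 40 admissions per month × 0.75 on antimicrobials × 6 months = 180 per ICU, and 180 × 35 = 6300. Both reproduce and neither is in dispute. No figure is given for this indicator.

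**Step 1: can the model be fitted without baseline stop dates?** The segmented model described in Statistics is

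Y(t) = b0 + b1·t + b2·P(t) + b3·P(t)·(t − t0),

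where P(t) is 0 before and 1 from implementation at t0. I take three months as about 13 weekly points, and month 7 as about 4 more.

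With post-implementation points only, P(t) = 1 throughout, so the level-change column equals the intercept and the slope-change column equals time minus a constant. The model collapses to

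Y(t) = (b0 + b2 − b3·t0) + (b1 + b3)·t.

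Only these two sums can be estimated; b2 and b3 cannot be separated from b0 and b1. The rank of the design matrix (4 needed) is:

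| Pre points | Post points | Rank |
|---|---|---|
| 13 | 13 | 4 |
| 0 | 13 | 2 |
| 0 | 17 | 2 |
| 1 | 13 | 3 |
| 2 | 13 | 4 |

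Two pre-implementation points are the bare algebraic minimum and would say almost nothing about a secular trend.

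**Step 2: what if some baseline stop dates exist?** Let c0 be the share of prescriptions with a stop date at baseline and c1 the share after implementation. Let r1 be the overrun rate in prescriptions that would have a stop date anyway, and r2 the rate in those that gain one through the review. Suppose nothing about adherence changes. Then

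- before: r1
- after: [c0·r1 + (c1 − c0)·r2] / c1
- apparent shift: (c1 − c0)(r2 − r1) / c1.

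I set c1 = 0.80, the fidelity threshold. That is an approximation, since fidelity also needs the other three components and the 48-hour timing. The values of c0, r1 and r2 are assumptions; the protocol gives none.

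| c0 | Shift if r1 = 20%, r2 = 40% | Shift if r1 = 30%, r2 = 40% |
|---|---|---|
| 10% | +17.5 points | +8.8 points |
| 30% | +12.5 points | +6.3 points |
| 50% | +7.5 points | +3.8 points |

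For example, with c0 = 0.30 and r1 = 20%: (0.06 + 0.20) / 0.80 = 32.5%, against 20% before. If r2 is smaller than r1, the sign reverses. If r1 = r2, there is no artefact.

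**The case against.** The strongest reply is that the protocol does not rule out baseline stop dates. Site selection criteria admits ICUs with an existing review below the 80% cut and measures review practice at patient level in the first two months. If adoption at baseline means reviews done in full, someone must check for a stop date. Implementation procedure mentions an E-CRF at baseline, and Data collection does not say that review data are recorded in months 4–6 only. A reader might infer from the timing that no pre-implementation series exists at all. The documents do not support that, and this part of the reply stands.

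A reader might also infer that the plan has chosen a denominator of documented prescriptions only. It has not: Table 2 is silent, and Statistics promises indicator definitions before data collection. A missing definition is not the complaint here. Nor do the documents support the idea that well-documented prescriptions are the better managed ones, so no direction of bias should be claimed.

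The reply does not remove the point. Wherever the protocol lists what is collected at baseline, the stop date is absent. A later definition can fix a denominator, but it cannot create data that were not collected. Leaving the choice of model to the data does not help either, because a level or slope change needs a pre-implementation series under any of the candidate models. Partial baseline stop dates lead to the selection problem of Step 2.

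**Conclusion.** The point holds in this form: the protocol assigns an interrupted time series to an indicator for which it provides no complete or comparable pre-implementation series.

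- **If no stop dates are captured before month 4**, level and slope change cannot be estimated (rank 2 of 4). This rests only on the model as described.
- **If some are captured**, a level change may be a selection artefact: 3.8 to 17.5 points in the illustrations, with unknown sign in practice. The size rests on assumed inputs. The mechanism needs only that overrun is judged where a stop date exists, that the review raises that share, and that overrun differs between the two groups.

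It would be wrong to read this as undermining the effectiveness analysis as a whole. Antimicrobial density, duration of therapy and redundancy, which carry the 10% targets, do not need a stop date, and neither the primary composite nor its thresholds depend on this analysis. The running-text list of care processes under Secondary outcomes omits the indicator altogether. The change should be made, but it is confined to one care-process measure.

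**What to change.** First, reconcile Implementation procedure with Data collection, and state whether stop dates are captured in months 1–3, by whom and on which form. Then choose one of two routes.

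1. **Exempt this indicator from the interrupted time series.** Report it descriptively for months 4–6 over all antimicrobial prescriptions, in three categories: stop date documented and kept, documented and exceeded, not documented. This needs changes of wording in Table 2 and Statistics and no new data. The price is that there is no before-and-after estimate for this indicator.
2. **If stop dates are captured from month 1, say so in Data collection** and run the time series with the same all-prescription denominator and the same three categories. The three series should be read together, because the documented-and-exceeded share can rise simply because more stop dates are written. If capture is not already in place, this route adds baseline data collection.

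Under either route, state that the detailed series ends with month 6 unless the registry collectors also take over the stop date.
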